## Abstract

**Background:**

As the incidence of stroke has increased, its impact on society has increased accordingly, while it continues to have a major impact on the individual. New strategies to further improve the quality, efficiency and logistics of stroke services are necessary. Early discharge from hospital to a nursing home with an adequate rehabilitation programme could help to optimise integrated care for stroke patients.

The objective is to describe the design of a non-randomised comparative study evaluating early admission to a nursing home, with multidisciplinary assessment, for stroke patients. The study is comprised of an effect evaluation, an economic evaluation and a process evaluation.

**Methods/design:**

The design involves a non-randomised comparative trial for two groups. Participants are followed for 6 months from the time of stroke. The intervention consists of a redesigned care pathway for stroke patients. In this care pathway, patients are discharged from hospital to a nursing home within 5 days, in comparison with 12 days in the usual situation. In the nursing home a structured assessment takes place, aimed at planning adequate rehabilitation. People in the control group receive the usual care. The main outcome measures of the effect evaluation are quality of life and daily functioning. In addition, an economic evaluation will be performed from a societal perspective. A process evaluation will be carried out to evaluate the feasibility of the intervention as well as the experiences and opinions of patients and professionals.

**Discussion:**

The results of this study will provide information about the cost effectiveness of the intervention and its effects on clinical outcomes and quality of life. Relevant strengths and weaknesses of the study are addressed in this article.

**Trial registration:**

Current Controlled Trails ISRCTN58135104

## Background

By the year 2020, 250 per 100,000 patients in the Netherlands will suffer from a stroke, and in many instances this will result in permanent disabilities and handicaps[1]. Substantial evidence is available showing that hospital stroke units reduce mortality, dependence and institutionalisation[2] and that better outcomes are associated with comprehensive and early assessment of stroke patients[3]. It is also suggested that organised integrated stroke care and the use of early supported discharge services for stroke patients are less expensive than general medical care, due to a reduction in hospital stay[4,5]. However there are very few data on the cost effectiveness of integrated stroke care from a societal point of view[6].

In the Netherlands 32% of stroke patients return directly to their home after hospital stay, 9% are discharged to a rehabilitation centre and 31%, mainly elderly stroke patients, are discharged to a nursing home for rehabilitation[7]. Consequently, contrary to nursing homes in many other countries, Dutch nursing homes fulfil an important role in the rehabilitation of stroke patients[8]. The mean duration of hospital stay of stroke patients in 2004 was 12.6 days[9]. Demographic developments, the increased incidence and prevalence of stroke, the emergence of disease management programs, and changes in the structure of the Dutch health care system have led to new strategies to further improve the quality, efficiency and logistics of care processes. Optimizing stroke services involves: a) faster admission of stroke patients to the hospital, leading to improved chances for effective intervention, b) early discharge from hospital, with an adequate plan for rehabilitation and c) improving care after discharge to home.

In 2006, these developments led to a redesign of the Stroke Service Maastricht Heuvelland. The essentials of this redesign are: stroke patients are admitted to Maastricht University Medical Centre for a maximum of 5 days for diagnosis, early intervention and stabilization, after which they are discharged to a special assessment and rehabilitation ward in a nursing home. In this nursing home, stroke patients undergo a structured multidisciplinary assessment, lasting a maximum of 5 days, and take part in their first rehabilitation activities. During assessment, the appropriate follow-up treatment is determined. Patients are then admitted to the follow-up setting for rehabilitative care. This means discharge to either their own home situation, to a specific rehabilitation hospital, or continued stay in the nursing home for prolonged rehabilitation or continuing stay.

Cost effective integrated stroke care requires a high degree of coordination between professionals in hospitals, nursing homes and home care, a high quality integral assessment in the nursing home and a system of adequately timed patient transitions.

The principal expectation is that the redesigned process of the Stroke Service Maastricht Heuvelland will lead to cost effective care, with expected improvement in the quality of care as well.

This article describes the design of a longitudinal comparative study, evaluating the cost effectiveness of an early discharge to and assessment of stroke patients in a nursing home, as part of a redesigned integrated stroke care programme, in comparison with a comparable stroke service region, where the redesign has not been implemented.

The research questions in this study are:

1. What is the effect of early admission to and assessment in the nursing home on functional outcomes, quality of life, and satisfaction with care in comparison with the usual care provided by a stroke service?[Effect evaluation]

2. From a societal perspective, what is the incremental cost effectiveness of early admission to and assessment in the nursing home, in comparison with the usual care provided by a stroke service?[Economic evaluation]

3. Research questions for the process evaluation

a) Is the new care pathway executed on time according to the protocol?[Process evaluation]

b) What are the experiences and opinions of patients and professionals about the newly developed care pathway?[Process evaluation]

## Methods/Design

### Study Design

We will conduct a comparative study with retrospective and prospective parts, in which we will compare the redesigned stroke service in the intervention region with a comparable region that offers the usual stroke care.

### Ethical approval and informed consent

The Medical Ethical Committee of the University of Maastricht has granted ethical approval. The trial is registered as ISRCTN58135104.

An information brochure will be given to all eligible patients. At inclusion, patients will be informed personally and also by means of written information on all aspects of the project. The privacy of the participating patients is protected, and all data will be coded and processed anonymously. It will be made clear in the informed consent form that each patient can terminate his or her participation in the trial at any moment without the care being influenced.

### Study population

The patient population consists of consecutive stroke patients who are admitted to the hospitals in both research regions during a period of 18 months. The diagnosis of stroke will be made by a neurologist based on patient history, physical examination and neuro-imaging. Patients will be eligible to participate if they meet the following criteria: over 18 years of age and fluent in Dutch. Exclusion criteria are: a life expectancy of less then a few days, a previous diagnosis of dementia, hospital discharge to home within a few days and occurrence of complications which require prolonged hospital care. Patients suffering a recurrent stroke during their participation in this study will not be asked to participate a second time.

### Sample Size

The primary goal of this study is to achieve cost reduction without loss of quality of life. Based on an earlier study among stroke patients[10], we estimate a difference in utilities indicating health related quality of life between the 2 regions. In this earlier study by Olsen, the utility difference based on the EuroQol was 0.11. Based on a power of 80%, alpha 0.05, our study will need a sample size of 111 participants per group.

We expect a 25% drop-out of patients between inclusion and the follow-up meeting 26 weeks later, due to premature termination of the trial participation, inability to cooperate in the trial, or mortality[11]. To correct for this expected drop-out, the number of patients included will be increased to 139 participants per group.

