### Effect evaluation

The primary outcome measures of the effect evaluation are quality of life and activities of daily life (ADL). Quality of life is measured by means of the Stroke Adapted Sickness Impact Profile 30 (SA-SIP 30)[12] and ADL by means of the Barthel index (BI)[13,14].

Secondary outcome measures are: instrumental activities of daily living (IADL) measured by means of the Frenchay Activity Index (FAI)[15], handicap measured by means of the Modified Rankin Scale (MRS)[16]. Cognitive functioning is measured by means of Mini Mental State Examination (MMSE)[17], Apraxia Test (AT)[18] and Star Cancellation Test (SCT)[19]. Anxiety and depression are measured by the Hospital Anxiety and Depression Scale (HADS)[20] and the patients' satisfaction with stroke care is measured by means of the Satisfaction with Stroke Care Questionnaire (SASQ-19)[21]. The strain on caregivers is measured by the Caregivers Strain Index (CSI)[22].

Other secondary outcome measures are medical complications occurring within 3 months after stroke. The following diagnoses are regarded as medical complications: a new stroke, epileptic seizures, pneumonia, urinary tract infections, fractures, bedsores, myocardial infarct, heart failure and atrial fibrillation. The data on medical complications will be collected from the patients' files.

Besides the primary and secondary outcome measures we assess some background variables which are considered to be predictors, confounders or effect modifiers. The following personal characteristics are assessed: age, sex, socio-economic status, risk factors, co-morbidity, stroke location and stroke severity measured by the National Institute of Health Stroke Scale (NIHSS)[23]. All background variables are measured at baseline.

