### Effect analysis

For the analyses we will use SPSS statistical software and Excel (for the Bootstraps). Missing data on the item level will be handled using SPSS missing value analysis. If considerable data are missing related to specific instruments, imputation will be considered.

A baseline analysis will be performed to examine the comparability of groups at baseline for both costs and outcomes. If necessary, methods will be applied to correct for differences in baseline[30]. A Kolmogorov-Smirnov test will be performed to investigate whether the data are normally distributed. If the data are distributed normally, our primary analysis will start with a t-test. If data are skewed, the primary analysis will be based on a non-parametric test for assessing two independent samples, i.e. a Mann-Whitney U test.

As it is known that in non-randomised comparative studies, variations in case mix between centres can influence the interpretation of outcome data[31], we would like to explore this in further analysis. Therefore, for each of the data sets collected at all measurement points, differences in outcome variable between the 2 regions will be tested using multiple MANCOVAs, entering various indicators of case mix as co-variates, i.e. age, gender, stroke severity. In addition, information on possible confounding factors and effect modifiers will be collected and analysed.

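### The stated 80% power is for a difference in EuroQol utility, not for SA-SIP30 or Barthel, and without a margin a non-significant difference test cannot support the no-loss goal

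*Protocol article*

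**What the plan says.** Four statements in the protocol article have to be read together.

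- **Goal (Sample Size).** "The primary goal of this study is to achieve cost reduction without loss of quality of life".
- **Sizing (Sample Size).** The calculation targets a difference: "we estimate a difference in utilities indicating health related quality of life between the 2 regions". The value comes from an earlier study among stroke patients, in which "the utility difference based on the EuroQol was 0.11". The result is: "Based on a power of 80%, alpha 0.05, our study will need a sample size of 111 participants per group". Allowing for drop-out ("We expect a 25% drop-out of patients between inclusion and the follow-up meeting 26 weeks later"), the target becomes "139 participants per group". The section gives no SD, no sidedness and no margin.
- **Primary outcomes (Effect evaluation).** "The primary outcome measures of the effect evaluation are quality of life and activities of daily life (ADL"), the first measured with the SA-SIP30 and the second with the Barthel index. EQ-5D is in neither the primary nor the secondary list there. Under Economic evaluation, SA-SIP30 is also the primary outcome of the cost-effectiveness analysis, and EQ-5D supplies the QALYs of the cost-utility analysis.
- **Primary test (Effect analysis).** "If the data are distributed normally, our primary analysis will start with a t-test"; for skewed data it is a Mann-Whitney U test. MANCOVAs with age, gender and stroke severity as covariates follow as further analysis.

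**The concern.** A goal of reducing costs with no loss of quality of life is a non-inferiority type of aim. To support it, the data must rule out a loss of some stated size. The plan gives a sample size for detecting a difference, and tests of difference, but names no size of loss to be ruled out.

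The power statement also concerns an outcome other than the declared primaries. No target difference, SD or power is given for SA-SIP30 or Barthel, so a reader cannot tell from the 80% how well the study can answer its primary effect question.

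The Discussion foresees broader implementation if the intervention appears cost effective. A no-loss statement feeding that decision should rest on a criterion that an imprecise study cannot meet simply by being imprecise.

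**Working it through.** **Inputs from Sample Size:** difference 0.11, power 80%, alpha 0.05, 111 per group evaluable, 25% drop-out, 139 per group recruited. **Assumed:** the SD (not stated), a two-sided test (not stated), normal approximation, equal groups.

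**1. The plan's own figure.** n = 2·SD²·(1.960 + 0.842)²/δ². Without an SD, 111 cannot be reproduced. Solving for it: SD = 0.11·√(111/2)/2.802 = 0.2925. If alpha were one-sided, the same step with 1.645 + 0.842 = 2.486 gives SD = 0.330. With SD 0.2925 two-sided, n = 111, as stated.

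**2. Evaluable number.** 139 = 111 × 1.25. With 25% drop-out, 139 × 0.75 = 104 per group remain.

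**3. What 80% power means for SA-SIP30 and Barthel.** Detectable standardised difference = 2.802·√(2/n), two-sided 0.05:

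| n per group | 80% power at | power at 0.30 SD | power at 0.20 SD |
|---|---|---|---|
| 111 | 0.376 SD | 61% | 32% |
| 104 | 0.389 SD | 58% | 30% |

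These cannot be turned into scale points, because the article gives no SD for either instrument.

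**4. What the same n means for a no-loss question on EQ-5D utility.** Non-inferiority power at a true difference of zero, one-sided 0.025 (lower limit of a 95% CI) = Φ(margin/SE − 1.960), with SE = SD·√(2/n). For SD 0.2925, SE = 0.0393 at 111 and 0.0406 at 104. The margins are illustrative, since the article states none:

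| margin | SD 0.2925, n = 111 | SD 0.2925, n = 104 | SD 0.33, n = 111 | evaluable n per group for 80% (SD 0.2925) |
|---|---|---|---|---|
| 0.05 | 25% | 23% | 20% | 538 |
| 0.08 | 53% | 50% | 44% | 210 |
| 0.10 | 72% | 69% | 62% | 135 |
| 0.11 | 80% | 77% | 70% | 111 |

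**5. Why a non-significant test is not enough.** With SD 0.2925, the 95% CI half-width is 1.96 × 0.0393 = 0.077 at 111 and 1.96 × 0.0406 = 0.080 at 104. An observed utility loss of 0.07 gives z = 0.07/0.0393 = 1.78 (p = 0.075) and z = 0.07/0.0406 = 1.73 (p = 0.084). Both are non-significant, yet the interval reaches a loss of about 0.15, beyond the 0.11 used for planning.

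**The case against.** Several points on the other side stand.

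- **Research question 1 is open.** It asks what the effect is, and difference tests fit that. They do not fit the no-loss goal, which is the one placed at the head of the sample size.
- **EQ-5D is not foreign to the study.** The article treats utilities as an indicator of health-related quality of life, and they feed the QALY, the primary cost-utility outcome. So it would go too far to say that the 80% bears on nothing in the study. However, the QALY is an area under the curve, so a single utility difference of 0.11 does not size it directly, and the effect evaluation measures quality of life with SA-SIP30.
- **The plan does not say that a null test will be read as no loss.** A reader might infer this from the goal and the tests together, but no section gives a rule for interpreting a non-significant result. Economic analysis also plans bootstrapping of the joint cost and effect differences, a cost-effectiveness plane and an acceptability curve. That is estimation and does not depend on p > 0.05, but it supplies no tolerated loss either.
- **Multiplicity.** A reader might infer an inflated error rate from two primary outcomes. That needs a rule that either outcome alone may carry the claim. The article states none, and such handling may sit in an analysis plan not shown.
- **A margin might be in a fuller document.** That is possible. The point here is that the goal, the sizing and the primary outcomes as printed do not fit together, and that 0.11 is presented as a difference, not as an acceptable loss.

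**Conclusion.** The point holds in this form: the 80% power refers to EQ-5D utility and not to SA-SIP30 or Barthel, and the planned primary test cannot by itself establish no loss. This follows from the text and needs no assumption.

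The detectable differences of 0.38 SD (111 per group) and 0.39 SD (104) assume only a two-sided 0.05 test and the normal approximation. The utility figures also rest on a back-solved SD of about 0.29, or 0.33 if the original alpha was one-sided, and on margins chosen for illustration.

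One might infer from the 80% at a margin of 0.11 that the planned numbers already suffice for a non-inferiority claim. The document does not support that. It needs the whole planning difference to be accepted as a tolerable loss, and 111 evaluable patients per group. At the 104 expected, power is about 77% with SD 0.29, and at any smaller margin it is lower.

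**What to change.** In Sample Size and Effect analysis:

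1. State that the 80% power refers to a difference of 0.11 in EQ-5D utility, and give the SD and sidedness used.
2. For SA-SIP30 and Barthel, give the standardised difference detectable with 80% power at two-sided 0.05: about 0.38 SD at 111 and 0.39 SD at 104 per group.
3. Name the quality-of-life outcome that carries the no-loss claim. Conclude no loss only if the 95% CI for the case-mix-adjusted difference on it excludes a loss as large as a margin that the sponsor pre-states and justifies. The covariates already listed for the MANCOVAs can serve for the adjustment. The direction must be stated too, because a higher SA-SIP30 score means worse quality of life.
4. Restate the power for that outcome and margin at the evaluable number expected.

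This is a change of wording. Its price is that the sponsor must commit to a margin, and that a null result alone no longer supports the claim. If the chosen margin is tight, the restated power may be low, and the sponsor would then have to accept that or reconsider the sample size.

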### Economic evaluation

The economic evaluation compares costs and outcomes of stroke care given in the Stroke Service Maastricht Heuvelland to care as usual provided by the Stroke Service Eindhoven. The economic evaluation will involve a combination of a cost-effectiveness analysis (CEA) and a cost-utility analysis (CUA). In a CEA effects are presented in clinical outcomes.

The primary outcome measure of the cost-effectiveness analysis will be the SASIP-30. Within the cost-utility analysis, outcomes will be measured by means of the standard Dutch version of the EuroQol (EQ-5 D)[24]. This is a self-administered questionnaire, which will be completed together with the cost questionnaire at 12 weeks and 26 weeks.

Both generic quality of life, as well as utilities, will be derived by means of the EQ-5 D. The EQ-5D is chosen because it is a widely used quality of life instrument. The EQ-5D contains 5 dimensions of health-related quality of life; mobility, self-care, daily activities, pain/discomfort and anxiety/depression. Each can be rated at three levels: no problems, some problems and major problems. The 5 dimensions can be added to comprise an overall health state. This health state will be translated into a number, a utility. Utility values can be calculated for these health states, using preferences elicited from a general population, the so-called Dolan algorithm[25]. The utility values derived from the Dolan algorithm will be used to compute Quality Adjusted Life Years (QALYs). The Dolan algorithm has been established using a general population from the UK. Recently a Dutch algorithm has become available, and this will be used in the sensitivity analysis[26]. The utilities at the two time points are used to compute a Quality Adjusted Life Years (QALY) score by means of the area under the curve method. Furthermore, the EQ-5D consists of a visual analogue scale (VAS) ranging from zero (worst imaginable health state) to 100 (best imaginable health state). The reliability and validity of the EQ-5D has been established[27]. The primary outcome measure for the cost-utility analysis will be Quality Adjusted Life Years (QALYs), based on the EuroQol utility scores[24,27]. In the CUA, the incremental cost-effectiveness ratio (ICER) will be expressed as the incremental costs per QALY. This economic evaluation will be performed from a societal perspective, which implies that all relevant costs and outcomes will be taken into account.

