#### Modified Rankin Scale (MRS)

The Modified Rankin Scale is a widely used instrument that measures levels of handicap. It defines 6 levels of disability, ranging from 0 (no symptom) to 5 (severe disability, bedridden, incontinent and receiving constant nursing care and attention)[16].

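### Deaths count as drop-out and mortality is not an outcome, so the Rankin and utility comparisons, and by implication the QALYs, are among survivors and could hide or reverse a mortality difference

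*Protocol article*

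**What the plan says.** All references are to the protocol article.

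- **Sample Size.** The planning effect comes from an earlier study in which "the utility difference based on the EuroQol was 0.11". This gives 111 patients per group. The 25% loss by week 26 is "due to premature termination of the trial participation, inability to cooperate in the trial, or mortality", and to make up for it "the number of patients included will be increased to 139 participants per group".
- **Effect evaluation.** The primary outcomes are the SA-SIP30 and the Barthel index. The secondary outcomes are named one by one, and then: "Other secondary outcome measures are medical complications occurring within 3 months after stroke". Nine diagnoses follow. Death is in none of these lists.
- **Modified Rankin Scale (MRS).** "It defines 6 levels of disability, ranging from 0 (no symptom) to 5". There is no category for death.
- **Economic evaluation and Table 1.** The EQ-5D is self-completed at 12 and 26 weeks. "The utilities at the two time points are used to compute a Quality Adjusted Life Years (QALY) score", by the area-under-the-curve method. No value is stated for a patient who has died.
- **Effect analysis.** There is one general rule for missing data, with imputation to be considered if much is missing. Death is not separated from other loss.
- **Economic analysis.** Resource use comes from professionals' registrations combined with a cost questionnaire at 12 and 26 weeks. The ICER uses costs and effects at 26 weeks. There is no rule for deaths.

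**The concern.** Death before week 26 is a known outcome, not an unknown one. Treating it as a loss to be replaced by extra enrolment leaves every comparison that needs a completed instrument among those still alive.

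This matters more here than in many studies. The Sample Size section states the aim as lower cost with quality of life preserved, and the intervention shortens the hospital stay to 5 days, from 12 (Abstract) or 10 (Usual care). A claim that nothing is lost has to be able to see deaths. The regions are not randomised, so mortality may also differ through case mix. If it does, a survivor comparison mixes the effect on patients' condition with the effect of who is left to be measured.

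**Working it through.** **1. The plan's own figure.** The article gives the difference (0.11), power (80%) and alpha (0.05), but no SD. With n = 2(1.96 + 0.8416)²·SD²/0.11², taken as two-sided, 111 per group implies SD = 0.2925. The step to 139 is 111 × 1.25 = 138.75. (Dividing instead, 111/0.75 = 148; that is a separate matter.) So 111 is the number meant to remain after deaths have been removed together with withdrawals. The share of the 25% that is mortality is not given.

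**2. Which patients can supply data.** A patient who dies before week 12 has no EQ-5D value. One who dies between weeks 12 and 26 has one of the two. Neither has a 26-week utility or, on the scale as described, a 26-week Rankin grade.

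**3. What a survivor comparison hides.** The article gives no mortality rate and no utility level, so both are assumptions here. With survivor mean u in both regions and death valued at 0, the all-patient mean is (1 − m)·u.

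| Assumed u | Mortality | Survivor difference | All-patient difference | Share of 0.11 |
|---|---|---|---|---|
| 0.60 | 10% vs 15% | 0 | 0.60 × (0.90 − 0.85) = 0.03 | 27% |
| 0.60 | 10% vs 20% | 0 | 0.60 × (0.90 − 0.80) = 0.06 | 55% |
| 0.65 | 10% vs 20% | 0 | 0.65 × (0.90 − 0.80) = 0.065 | 59% |

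With equal mortality and equal u, both differences are 0 and nothing is hidden.

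**4. How the sign can reverse.** Take two identical populations. In one, 10% die and survivors average 0.65. In the other, a further fraction x dies, whose utility would have been 0.20. The second region's survivor mean is (0.90 × 0.65 − 0.20x)/(0.90 − x).

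- x = 5%: (0.585 − 0.010)/0.85 = 0.676, which is 0.026 **higher**. The all-patient mean is 0.05 × 0.20 = 0.010 **lower**.
- x = 10%: (0.585 − 0.020)/0.80 = 0.706, which is 0.056 **higher**. The all-patient mean is 0.10 × 0.20 = 0.020 **lower**.

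In this set-up the reversal occurs whenever the additional deaths are among patients whose utility would have lain between 0 and the survivor mean.

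**5. What scoring deaths as 0 does to the SD.** The variance is (1 − m)(s² + u²) − ((1 − m)u)². With s = 0.2925 (implied in step 1) and u = 0.65 (assumed), the SD is 0.339, 0.356 and 0.369 at mortality of 10%, 15% and 20%. The number needed for an all-patient difference of 0.11 becomes 150, 165 and 177 per group.

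**The case against.** The strongest reply is that the Sample Size sentence is an enrolment allowance and not an analysis rule. Patients who have died cannot attend a 26-week visit, so allowing for them is ordinary. Nothing in the article says that they are left out of the QALYs, the costs or the Rankin analysis, and a full protocol or SAP that is not shown may deal with them.

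Much of this stands, and it rules out some stronger readings that a reader might infer:

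- *No outcome scale can represent death.* This is not so for utilities and QALYs, which can take 0 for death. The article only fails to state that value.
- *The QALYs and the ICER are stated to be survivor-only.* They are not. This follows from the inputs named, but it is nowhere said outright.
- *Patients who die drop out of the costs.* This is not supported. Professionals' registrations are also a source, and a patient who dies after week 12 may have returned the first questionnaire.
- *Mortality is the main safety question because patients leave a week earlier.* The article does not say this. The shortening is 5 or 7 days, depending on the section. Discharge requires medical stability, and patients with a very short life expectancy or with complications needing prolonged hospital care are excluded. New stroke, pneumonia, myocardial infarct and heart failure are recorded.

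It is also fair that a Rankin grade for death is a convention of analysis and not part of the instrument as described, and that the SA-SIP30 and the Barthel index have no natural value for death.

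The reply does not reach what the article does fix: death is classed with withdrawal, the sizing rests on those who remain, the Rankin scale ends at 5, and the outcome lists omit mortality. An SAP that valued death at 0 would depart from the basis on which 111 and 139 were set.

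**Conclusion.** The point holds in a limited form and should be corrected. It is firmest for the sample-size basis, the outcome list and the Rankin scale. For the utility comparison it follows from self-completion and the drop-out definition. For the QALYs and the ICER it holds by implication only. The primary SA-SIP30 and Barthel comparisons share the problem.

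The size and direction of any bias cannot be known from the document. The 0.03 to 0.06 hidden out of 0.11 assumes a survivor utility of 0.60 in both regions and mortality of 10% against 15% to 20%. The reversal also assumes that the extra deaths fall on patients with low utility. These figures show what could happen; they do not predict this study's result.

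**What to change.** 1. Add 26-week mortality by region as a reported outcome, as an estimate with a confidence interval. With 139 per group, the power to detect 10% vs 20% is about 65%, and for 10% vs 15% about 24%, so a non-significant test would not be reassuring.
2. In the QALY area under the curve, set utility to 0 from the date of death. No EQ-5D is taken before week 12, so also state the utility assumed for time alive before then.
3. Count costs up to death from the professional registrations already planned, and zero afterwards. The article bases professionals' intervention time on a random sample, so check that the registrations cover each patient who dies.
4. Analyse the Rankin scale with death as an added worst category.
5. For the SA-SIP30 and the Barthel index, report survivors with mortality alongside, plus a sensitivity analysis giving deaths the worst rank. The Mann-Whitney test already named can carry this.
6. Restrict drop-out to withdrawal and inability to cooperate, and state the expected mortality separately.

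**Cost.** Most of this is wording in the analysis plan. Two items are not. Vital status and date of death must be collected to 26 weeks in both regions, while the planned file review for complications stops at 3 months. And although patients who die now count as evaluable, scoring them as 0 raises the SD (150 to 177 per group under the assumptions above, against 139 enrolled), so the power for the 0.11 difference should be rechecked and restated.

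### The 25% drop-out allowance multiplies 111 by 1.25 instead of dividing by 0.75, so 139 per group gives about 77% power, not the stated 80%, for the EuroQol planning difference

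*Protocol article*

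**What the plan says.** All the figures stand in the Sample Size section of the protocol article.

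- Planning difference, taken from an earlier stroke study: "the utility difference based on the EuroQol was 0.11".
- Requirement before drop-out: "Based on a power of 80%, alpha 0.05, our study will need a sample size of 111 participants per group".
- Expected loss: "We expect a 25% drop-out of patients between inclusion and the follow-up meeting 26 weeks later". The same sentence gives the reasons as early withdrawal, inability to take part, and death.
- Inclusion target: "To correct for this expected drop-out, the number of patients included will be increased to 139 participants per group".

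The section gives no standard deviation and does not say whether alpha is one- or two-sided. No other section of the article gives a different drop-out allowance or inclusion target.

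**The concern.** The section defines drop-out as a share of the patients included. The number to include must therefore be large enough that 75% of it equals 111. The stated 139 instead adds 25% of the 111 completers, which is a smaller quantity.

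The requirement, the expected loss and the inclusion target therefore cannot all hold together with 80% power. If every planning assumption turns out to be exactly right, including the 25% loss, the study still ends with fewer evaluable patients than the section says it needs. The section describes the aim as reducing costs without losing quality of life. Under such an aim, a power figure that is too favourable matters somewhat, because a non-significant utility difference may be read as reassurance.

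**Working it through.** **Inputs (all from Sample Size).** Evaluable patients needed: 111 per group. Expected loss from inclusion to 26 weeks: 25%. Stated inclusion: 139 per group. Power 80%, alpha 0.05, utility difference 0.11. Assumptions not in the article: a two-sided test (one-sided also shown) and a comparison of two means with equal groups.

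**1. Reproduce the stated figure.** n × (1 + d) = 111 × 1.25 = 138.75, rounded up to 139. This matches exactly.

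**2. Inflation that fits the definition of drop-out.** n / (1 − d) = 111 / 0.75 = 148. Check: 148 × 0.75 = 111. The gap is 148 − 139 = 9 per group, or 296 − 278 = 18 in total.

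**3. Evaluable patients that 139 leaves.** 139 × 0.75 = 104.25, so about 104 per group. The shortfall is 111 − 104 = 7 per group.

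**4. Largest loss that 139 can absorb.** 1 − 111/139 = 20.1%.

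**5. Power with 104 per group.** For a fixed difference and standard deviation, the expected test statistic scales with the square root of n. With 111 per group and 80% power it equals z(alpha) + z(0.80). With 104 per group:

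- Two-sided: (1.960 + 0.842) × √(104/111) − 1.960 = 2.802 × 0.968 − 1.960 = 0.752, and Φ(0.752) = 77.4%. The noncentral t distribution also gives 77.4%.
- One-sided: (1.645 + 0.842) × 0.968 − 1.645 = 0.762, and Φ(0.762) = 77.7%.

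The standard deviation cancels in step 5: only the ratio 104/111 and the stated 80% enter. The unstated standard deviation therefore does not affect the result, and the unstated sidedness changes it by about 0.3 points.

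**6. What cannot be checked.** Whether 111 is itself right depends on the missing standard deviation. Working back from 111, 0.11 and 80% power, a two-sided test implies a standard deviation of about 0.29. Assumed values from 0.25 to 0.35 would give 82 to 159 per group. The drop-out point takes 111 as given.

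**The case against.** The strongest reply is that the effect is small. The loss is 2 to 3 power points and about 7 evaluable patients per group. That is minor beside the uncertainty about the standard deviation in step 6, and the 25% is itself a forecast. This stands, and it sets the weight of the point: it should be corrected, but it does not undermine the design.

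Three defences of 139 do not stand.

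- **Deaths might still contribute data.** The section lists mortality among the reasons for the 25% and corrects for the whole of it.
- **Imputation might recover the losses.** Effect analysis says only that imputation will be considered if considerable data are missing for particular instruments. Sample Size relies on extra inclusions.
- **The 25% might refer to the 111.** The text counts losses from inclusion, so the base is the patients included.

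A reader might also infer two stronger things that the article does not support.

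- **That the primary effect outcomes fall short of their planned power.** The calculation concerns a EuroQol utility difference. Effect evaluation names the SA-SIP30 and the Barthel index as primary, and the EQ-5D belongs to the economic evaluation. The article states no power for the SA-SIP30 or the Barthel index, so the 77% says nothing about them.
- **That adjusting for baseline covariates would make up the shortfall at no cost.** Under balanced covariates, a multiple correlation of about √(1 − 104.25/111) = 0.25 with the outcome would be enough. Balance cannot be assumed in a non-randomised comparison of two regions, and Effect analysis itself allows for case-mix differences. As an illustration with an assumed figure, a regional difference of 0.5 standard deviations in one covariate gives R² = 0.25/4.25 = 0.059 for region on that covariate. That inflates the variance of the adjusted difference by 1/(1 − 0.059), or about 6%, which cancels nearly all of the roughly 6% gain. Table 1 also shows no EQ-5D or SA-SIP30 at T0, so these outcomes cannot be adjusted for their own baseline.

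**Conclusion.** The inclusion target is wrong as written and should be fixed. Given the article's own requirement of 111 and its own 25% loss, 139 per group leaves about 104 evaluable patients. Power for the planning difference of 0.11 in EuroQol utility is then about 77%, not 80%. The number that keeps 80% is 148 per group; 139 keeps it only if loss is at most about 20%.

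The completer count needs no assumption beyond the stated figures. The power figure assumes a two-sided comparison of two means and takes 111 as correct for 80%. The conclusion is limited to the utility comparison used for planning and does not extend to the SA-SIP30 or the Barthel index.

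**What to change.** Rewrite the last sentence of Sample Size. Keep 139 per group, and state that at 25% drop-out it yields about 104 evaluable patients per group and about 77% power for a utility difference of 0.11, with 80% power only if drop-out is at most about 20%. Add that 148 per group would be needed to keep 80% at 25% drop-out. State the sidedness of alpha in the same sentence, since the power figure assumes it.

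This costs one sentence and no extra patients; the only downside is a slightly less favourable stated power. If the sponsor prefers to keep 80%, the cost is 9 more inclusions per group, 18 in total.
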